## Abstract

**Background:**

Despite the proven benefits of exercise in older adults, challenges such as access and motivation can deter their engagement. Interactive virtual reality (VR) games combined with exercise (exergames) are a plausible strategy to encourage physical activity among this population. However, there has been little research on the feasibility, acceptability, and potential benefits of deploying at-home VR exergames among community-dwelling older adults.

**Objective:**

The objectives of this study are to estimate the feasibility, usability, and acceptability of a co-designed VR exergame in community-dwelling older adults; examine intervention feasibility and assessment protocols for a future large-scale trial; and provide pilot data on outcomes of interest (physical activity, exercise self-efficacy, mood, cognition, perception, and gameplay metrics).

**Methods:**

The study will be a remote, 6-week intervention comprising an experimental and a control group. A sample of at least 12 community-dwelling older adults (with no or mild cognitive impairment) will be recruited for each group. Both groups will follow the same study procedures and assessment methods. However, the experimental group will engage with a co-designed VR exergame (*Seas The Day*) thrice weekly for approximately 20 minutes using the Oculus Quest 2 (Facebook Reality Labs) VR headset. The control group will read (instead of playing *Seas The Day*) thrice weekly for approximately 20 minutes over the 6-week period. A mixed methods evaluation will be used. Changes in physical activity, exercise self-efficacy, mood, cognition, and perception will be compared before and after acute data as well as before and after the 6 weeks between the experimental (exergaming) and control (reading) groups. Qualitative data from postintervention focus groups or interviews and informal notes and reports from all participants will be analyzed to assess the feasibility of the study protocol. Qualitative data from the experimental group will also be analyzed to assess the feasibility, usability, and acceptability of at-home VR exergames and explore perceived facilitators of and barriers to uptaking VR systems among community-dwelling older adults.

**Results:**

The screening and recruitment process for the experimental group started in May 2021, and the data collection process will be completed by September 2021. The timeline of the recruitment process for the control group is September 2021 to December 2021. We anticipate an estimated adherence rate of ≥80%. Challenges associated with VR technology and the complexity of remote assessments are expected.

**Conclusions:**

This pilot study will provide important information on the feasibility, acceptability, and usability of a custom-made VR exergaming intervention to promote older adults’ well-being. Findings from this study will be useful to inform the methodology, design, study procedures, and assessment protocol for future large-scale trials of VR exergames with older adults as well as deepen the understanding of remote deployment and at-home use of VR for exercise in older adults.

**International Registered Report Identifier (IRRID):**

DERR1-10.2196/32955

## Introduction

### Background

Population aging is a global phenomenon. With the increase in global life expectancy (average of 73.4 years in 2019) and all baby boomers reaching >65 years of age in 2031 [1], the proportion of older adults (aged ≥60 years) is estimated to nearly double (from 12% to 22%) and increase to upwards of 2 billion individuals by 2050 worldwide [2]. The number of *oldest-old* individuals (aged ≥80 years) is increasing even faster and is expected to triple by 2050 [3]. With such a drastic shift in global population demographics, the incidence of chronic conditions and cognitive impairment is also expected to increase exponentially, leading to higher rates of disability and dependency worldwide [4-6]. In addition to decreased functional ability, cognitive changes, specifically in executive function, pose significant health and social challenges to older adults’ everyday lives and independence [7-9]. This warrants research focused on strategies to foster healthy aging and reduce the impact of age-related changes in older adults’ functional and cognitive abilities.

Physical activity is an established predictor of healthy aging and is associated with numerous physical and psychological health benefits in older adults. Incorporating physical activity into daily life can improve older adults’ motor function, mood, cognition, quality of life, and independence [10-12]. An extensive body of literature has highlighted the positive effects of physical activity on older adults’ executive functions, including processing speed, attention, inhibition, and working memory [13,14]. In particular, both a single bout of aerobic exercise and a period of aerobic exercise training have been shown to promote brain health and executive function in the older population [12,15-17]. Physical activity has also been recognized as a valuable part of preventative and therapeutic strategies for older adults living with mild cognitive impairment and people living with dementia [12,18-21]. Despite strong evidence supporting the broad physical and mental benefits of physical activity, older adults tend to be the least physically active age group, and few older adults are sufficiently active to meet the physical activity guidelines [22]. Lack of motivation and enjoyment, limited access to exercise programs or equipment, and physical limitations are some of the main reasons cited for physical inactivity among older adults [23]. For those living with cognitive impairment, physical activity participation and adherence are particularly restricted because of health challenges associated with the condition as well as poor self-efficacy, apathy, and poor access to exercise opportunities that meet their needs and capabilities [24-26].

### Physical Activity in the Era of the COVID-19 Pandemic

Barriers to physical activity have been exacerbated during the COVID-19 pandemic. Countries have implemented public health measures, including program and facility closures, to contain COVID-19 infection and reduce its health, social, and economic impacts. Older adults are considered a highly vulnerable population to the impact of the COVID-19 outbreak and have faced stricter restrictions than other age groups [27,28]. Staying physically active during the COVID-19 pandemic is more difficult but is particularly important as physical activity is a protective factor against viral infections [29,30]. In addition, engaging in physical activity can be a moderating factor for mental well-being [31-33].

However, with physical distancing measures and the closure of exercise programs and fitness facilities in response to the COVID-19 pandemic, physical activity and exercise opportunities are more restricted for many older adults [34,35]. More optimistically, restrictions and changes in lifestyle as a result of COVID-19 have increased technology adoption among older adults [36-39]. Various opportunities for using novel information and communication technologies (eg, mobile apps, activity trackers, and gamified exercises) have emerged aiming to complement remote exercise programs and potentially benefit older adults’ health and well-being while mitigating social distancing [40,41]. From wearables to applied games, digitally connected technologies are now filling the gap in many in-person activities that cannot be conducted because of the COVID-19 pandemic [42].

When promoting at-home physical activity, exercise video games (also known as exergames) have been shown to be a viable supportive tool to enhance older adults’ well-being during the current pandemic [43-46]. Systematic reviews have shown that exergames have been successfully used to foster improvements in health-related outcomes such as pain management, posture, cognitive functioning, and decreased risk of falls among community-dwelling older adults [47]. Specific physical outcomes such as muscle strength, balance, mobility (including upper and lower limb flexibility), and cardiorespiratory fitness also improved after exposing prefrail and frail older adults to exergaming interventions [48]. Similar results were found in active older adults using exergames with floor-projected features [49]. Although Nintendo Wii and Microsoft Kinect are among the most used interactive systems, the use of immersive virtual reality (VR)—which includes a head-mounted display—is still scarce [50]. Advancements in hardware development, distribution, and accessibility are essential to increase the use of VR applications. The creation of more immersive VR technologies, which are now accessible and commercially available, has allowed for the distribution of VR-based exergames to aid the immersion and interaction of players in virtual environments and potentially create an engaging experience to encourage physical activity participation [51]. The main difference of VR exergames compared with traditional exergames is the use of head-mounted displays to provide a more immersive experience, potentially leading to a more consistent feeling of presence and agency [52]. However, deploying VR exergaming technology for older adults’ at-home exercise, especially during a pandemic, can be complex for various reasons, such as (1) technology access (eg, the cost is still similar to state-of-the-art video gaming consoles) [47], (2) technical complexities (eg, hardware calibration and launching the games as well as content appropriateness), (3) older adults’ technology literacy, and (4) challenges of remote deployment and testing to capture potential physical and mental outcome measures [52]. Moreover, although the multisensory environment of VR exergames can be tailored to the participants’ functional and cognitive abilities [53], research on preferences for VR activities and interactions among older adults and systematic evaluation of VR exergames is limited [54]. This makes the creation and deployment of home-based VR exergames for older adults challenging; and to our knowledge, it has not been done remotely before.

The long-term objective of our research is to develop and assess VR exergames that enable greater access to exercise opportunities for older adults. Therefore, the proposed pilot study aims to determine the feasibility, usability, and acceptability of a 6-week VR exergame intervention and the feasibility of the assessment protocol among community-dwelling older adults. Changes in potential outcomes for a larger-scale trial will also be explored, including physical activity, exercise self-efficacy, mood, cognition, and perception. The pilot gameplay data enable an exploration between game metrics and outcome performance, which will allow for the estimation of whether data from the game can be used for real-time assessments and other such applications.

## Methods

### Study Design

This is a 6-week pilot study to examine the feasibility, acceptability, and usefulness of a co-designed VR exergame intervention among older adults as well as the feasibility of the study procedures and assessment protocol. A control group will be used to account for practice and exposure effects and will follow the same protocol as that described for the experimental group without exposure to the exergame; they will read 3 times a week for 15 to 20 minutes instead of engaging with our exergames. To maintain consistency between the control and experimental conditions, the same questionnaires and surveys will be completed by all the participants in both groups, except for the *perceived enjoyment* and *rate of perceived exertion (RPE)* scales, which will be completed only by the experimental group. Both qualitative and quantitative methods will be used to provide pilot data on potential outcomes of interest. Although this study will evaluate the feasibility of both the study intervention and study control arms, we will not randomize the participants. Participants in the intervention arm will be recruited first, followed by a wave of participants recruited to the control group. The study is based in Waterloo but will be carried out remotely, so participants from across Canada will be eligible.

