### Study Sample and Recruitment

A combination of convenience and snowball sampling will be used for the purposes of this study. To be eligible, participants must be aged ≥60 years, living in a community setting in Canada, and able to communicate in English and provide consent on their own behalf. The participants must have access to a computing device (computer or tablet) and a reliable internet connection at their place of residence to complete the web-based assessments and tasks. Participants in both groups must be able to safely participate in light to moderate unsupervised activity without requiring a physician’s approval as assessed using the Get Active Questionnaire (GAQ) [55,56]. Exclusion criteria include (1) diagnosis of moderate or severe dementia or a score <18 on the Montreal Cognitive Assessment (MoCA; version 8.1-Telemed) [57,58]; (2) self-reported severe motion sickness or commonly experienced motion sickness or nausea when driving or sitting in a car, train, or bus; (3) self-reported hearing impairment that may interfere with the participant’s ability to hear and understand the auditory cues in the cognitive and perceptual tasks; (4) uncorrected visual impairment (eg, cataracts, glaucoma, or macular degeneration) that may interfere with the participant’s ability to see and interact with the game and perform the cognitive and perceptual tasks; (5) ear infection in the previous 12 months or a diagnosis of a disease of the middle ear, such as Meniere disease; and (6) any preexisting conditions that would prevent them from engaging in exercise, including having a cardiac pacemaker. The same inclusion and exclusion criteria will be used for both the experimental and control groups to ensure internal validity.

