#### Outcome Analyses

Descriptive statistics will be calculated for all demographic and baseline characteristics of the participants and presented as means and SDs or percentages (n), as appropriate. Assumptions underlying the statistical procedures will be checked, and corrective procedures will be used if necessary. Statistical analyses will be performed in R Studio (R Foundation for Statistical Computing) and SPSS (IBM Corporation). Data from the cognitive and perceptual tasks will be assessed for normality using *Q*-*Q* plots, the Shapiro-Wilk test, and histograms. Homogeneity of variance will also be tested using the Mauchly sphericity test, and Greenhouse-Geisser corrections will be applied if necessary. Potential deviations from a normal distribution will be identified in all cognitive and perceptual task data sets, and log transformations will be applied to the raw skewed data if deemed necessary to transform the data into a normal distribution. Paired and independent 2-tailed *t* tests will be used to compare the baseline, follow-up, and acute scores. Repeated-measure and mixed ANOVAs will be used to analyze before and after intervention data (exergaming or reading for 6 weeks) as well as acute data (before and after 1 bout of exergaming or reading) to understand changes by time (before and after), group (control vs experimental), and day (eg, weeks 2, 4, and 6 for SIFI) to compare baseline, follow-up, and acute scores.

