## Results

This study aims for an estimated adherence rate of ≥80%. To minimize potential attrition, all participants will be provided with a thorough remote one-on-one explanation of the anticipated participation burden (time commitment) at baseline. The participants will also be contacted regularly throughout the data collection process to maintain a good working relationship and answer any questions that they may have. The participants may choose to withdraw from the study at any time and for any reason. However, they will be asked if their collected data can be used by the research team for information and data analysis purposes.

We anticipate that most of the enrolled participants will adhere to the study and follow the protocol. However, potential challenges related to nausea and motion sickness when interacting with the VR technology may lead to some dropouts in the experimental group [105-108]. Challenges related to remote assessments as well as the length and complexity of the cognitive and multisensory integration tasks may also result in attrition [109-112].

In addition, we anticipate that most participants will learn how to navigate virtual environments and successfully perform the proposed physical activities within the different stages of our exergame [113,114]. This can potentially lead to high levels of perceived enjoyment and study adherence, as found in similar studies using immersive VR with the same duration and frequency [115]. However, it is also expected that some older adults might need more support than others to set up the VR system and adapt to the technology [113,114,116,117]. These supports might need to be individualized and tailored as the pilot progresses.

Both the experimental and control conditions have been reviewed and received ethics clearance through the University of Waterloo Research Ethics Committee (experimental condition ethics clearance in April 2021 and control condition ethics clearance in June 2021). The screening and recruitment process for the experimental group started in May 2021, and the data collection process will be completed by September 2021. As of August 16, 2021, 15 community-dwelling older adults have enrolled in the experimental group, of whom 2 (13%) have dropped out. The recruitment process and data collection for the control group will start in September 2021 and be completed by December 2021.

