### Strengths and Limitations

This study will establish the feasibility of deploying a VR system to older adults across Canada for health application purposes. This study will also assess the feasibility of a complex assessment protocol. Both may provide useful insights for the future of remote, virtual research and are specific not only to VR research but also more broadly applicable.

Reaching our target population may be challenging during the COVID-19 pandemic and will likely be restricted to older adults who are open to the use of technology and have the ability to do so (eg, have a computer or tablet and internet already). In addition, older adults may be hesitant to participate because of (1) technology apprehension, (2) availability of other physical activity options (as, at the time this paper was written, the restrictions had started to loosen up), and (3) time commitment (8 weeks total, with multiple tests and web-based meetings). We plan to minimize the impact of these limitations by carrying out introductory sessions to facilitate the usability of the technology at the beginning of the trial, using stand-alone VR systems that are portable and can be used without an internet connection, and building rapport with all the participants to facilitate a long-standing research relationship and reduce the burden of taking part in this research remotely.

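### The two arms are sequential, non-randomized waves, so between-arm differences in 6-week change (PASE above all) are confounded with calendar period and volunteer selection, and shared eligibility criteria do not remove this.

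*Protocol article*

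**What the plan says.** Under Study Design the protocol article says "we will not randomize the participants" and sets the order: "Participants in the intervention arm will be recruited first, followed by a wave of participants recruited to the control group". Study Sample and Recruitment describes convenience and snowball sampling.

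The Results section dates the waves. For the exergame arm: "The screening and recruitment process for the experimental group started in May 2021, and the data collection process will be completed by September 2021". For the reading arm: "The recruitment process and data collection for the control group will start in September 2021 and be completed by December 2021".

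Between-arm comparisons are planned all the same. The abstract says that changes in physical activity, self-efficacy, mood, cognition and perception will be compared "as well as before and after the 6 weeks between the experimental (exergaming) and control (reading) groups". Outcome Analyses lists, among the factors of the repeated-measures and mixed ANOVAs, "group (control vs experimental". The section on physical activity, self-efficacy and mood applies paired or independent t tests to the PASE.

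On comparability, Study Sample and Recruitment says: "The same inclusion and exclusion criteria will be used for both the experimental and control groups to ensure internal validity". Strengths and Limitations covers reach, lack of control over the home environment, small sample and self-report. It does not mention the sequential, non-randomized arms.

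**The concern.** One arm is followed from late spring into early autumn and the other from early autumn into winter, during a pandemic in which access to exercise was changing. The article's own introduction says that closures of programs and facilities restricted older adults' activity. The PASE asks about outdoor walking, sport and recreation, so it can plausibly move with weather and access whether or not anyone plays the game. Exercise self-efficacy and general affect may move too.

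Under convenience and snowball sampling the two waves may also differ in who comes forward. Common eligibility criteria fix who may enter. They do not fix who volunteers, or what happens around participants while they are followed. The closing clause of the eligibility paragraph therefore claims more than the design can deliver.

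At stake is the reading of the 6-week group comparison for a few secondary outcomes. Run as planned, the tests would yield a difference that cannot be attributed to the exergame, and nothing in the article tells the reader so.

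**Working it through.** The article gives no formal sample size calculation, so there is no figure to reproduce. The check is structural, followed by an illustration.

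**Inputs.** Exergame wave May to September 2021 and reading wave September to December 2021 (Abstract and Results); at least 12 per group (Sample Size); 8 weeks of commitment per participant (Strengths and Limitations); 15 enrolled in the exergame arm by 16 August 2021 (Results); assessment schedule (Table 2).

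**1. Calendar overlap.** September is the only month named for both arms, and it is the month by which exergame data collection is to finish and in which control recruitment is to start. The exergame arm had already passed its target of 12 before control recruitment was due to open. With 8 weeks per participant, the 6-week exposures do not overlap in any useful way.

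**2. Can arm and wave be separated?** Code arm a = 1 for exergame and 0 for reading. Wave is then p = 1 − a.
- Columns [1, a, p]: one exact dependency, so rank 2 of 3. The correlation of a and p is −1.
- Before/after model with time t, columns [1, t, a, p, a·t, p·t]: p = 1 − a and p·t = t − a·t are two dependencies, so rank 6 − 2 = 4 of 6.

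Write the mean 6-week change as practice + τ + π₁ in the exergame wave and practice + π₂ in the reading wave. Here τ is the exergame effect, and π₁ and π₂ collect period and selection. The difference between arms is τ + (π₁ − π₂). Change scores, baseline adjustment and the group-by-time term all estimate this sum and never τ alone. Entering calendar date as a continuous covariate would not help: with almost no common dates, the answer would rest on extrapolating an assumed trend.

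**3. Which outcomes are exposed?** From Table 2 and the analysis sections:

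| Outcome | Timing | Exposure |
|---|---|---|
| PASE | baseline and follow-up only | highest; no same-session contrast to fall back on |
| Exercise self-efficacy | baseline, then after sessions in weeks 2, 4 and 6 | high; no same-session before/after pair |
| PAAS, baseline to follow-up | 6-week change | exposed |
| PAAS, before/after a session | each week | low; a slow trend cancels within the session, though selection between waves remains |
| Flanker, OTMT, VF, RT, SIFI | baseline, follow-up and same-session pairs | 6-week change formally exposed; same-session contrasts little exposed |
| SJ, TOJ | baseline and follow-up only | formally exposed; a seasonal effect is less obvious |
| RPE, perceived enjoyment | exergame arm only | no arm comparison |
| Feasibility, usability, adherence | primary | do not need the arm contrast |

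**4. Illustration.** Take τ = 0, n = 12 per arm and a two-sided 5% two-sample t test with 2 × 12 − 2 = 22 df. For a period or selection shift of δ SDs of the analysed score, the noncentrality is δ√(n/2) = δ√6 ≈ 2.449δ. The rejection rate is the probability that a noncentral t exceeds the critical value in absolute size.

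| Assumed δ | Noncentrality | Rejection rate |
|---|---|---|
| 0 | 0 | 5.0% |
| 0.25 | 0.61 | 9.0% |
| 0.5 | 1.22 | 21.6% |
| 0.8 | 1.96 | 46.6% |
| 1.0 | 2.45 | 64.9% |

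The documents give no seasonal or reopening figure, so every δ above 0 is an assumption. The rates are the same for a shift of either sign.

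**The case against.** The strongest reply is that this is a feasibility pilot that openly says it is not randomized and dates both waves. Feasibility and usability are primary; activity, affect and self-efficacy are secondary and exploratory. The control group's stated role is to account for practice and exposure, and the article asks for caution in interpreting its statistics. Most of this stands, and it limits the severity. The call for caution does not answer the point, because it is tied to small sample size and self-report. The control group can still serve its stated role if practice and exposure effects are assumed not to vary by period.

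Four stronger readings are tempting, and the documents do not support them:
- *The article will claim an exergame effect on activity, or carry the arm difference forward as the later trial's effect size.* It says neither. Sample Size says only that the data will inform later calculations, which SDs and attrition would also satisfy.
- *All mood results are compromised.* The PAAS analysis is aimed mainly at acute, same-session change, which is little exposed.
- *The bias favours the exergame.* An autumn fall in activity among controls would do that, but reopening could raise their activity and work the other way.
- *The article admits that changing restrictions will affect outcomes.* The remark on "availability of other physical activity options (as, at the time this paper was written, the restrictions had started to loosen up" appears in a list of reasons why people might hesitate to take part. It shows that conditions were changing, but makes no statement about outcomes.

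The wording on internal validity can be read as a statement of purpose and not of achievement. Even so, the verb promises too much for sequential waves.

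**Conclusion.** The point holds at moderate severity. Arm and calendar wave cannot be separated in this design, so the planned between-arm comparisons of 6-week change cannot be attributed to the exergame. The consequence is greatest for the PASE, then exercise self-efficacy and the baseline-to-follow-up PAAS. Same-session contrasts are much less exposed and the primary feasibility outcomes are untouched.

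The non-separability follows from the article's own dates and needs no assumption beyond treating September 2021 as a hand-over month. The size and direction of the bias are unknown. The rejection rates of 9.0% to 64.9% belong to assumed shifts of 0.25 to 1.0 SD and are not estimates for this trial. The statement that shared criteria secure internal validity is too strong as written, and the limitations omit the main threat to these particular comparisons.

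**What to change.** 1. **Outcome Analyses, and the section on physical activity, self-efficacy and mood:** label the 6-week between-arm contrasts as descriptive. Report each as an estimate with a 95% CI, and state that it is confounded with calendar period and wave selection and will not be attributed to the exergame.
2. **Study Sample and Recruitment:** replace the closing clause on internal validity with, for example: *common criteria make the eligible populations comparable, but do not control for calendar period or for who volunteers in each wave.*
3. **Strengths and Limitations:** add sequential, non-randomized recruitment and calendar confounding, naming season and changing pandemic restrictions.
4. **Sample Size:** clarify that the pilot informs the larger trial through SDs, attrition and adherence, and not through the between-arm difference.

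The cost is wording only: no new arm, assessment or participant. The article places control recruitment after its 16 August 2021 enrolment count, so the relabelling could have been settled before any control data existed. The downside is a weaker claim for a few secondary outcomes.
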